#### Short term

(1) the proportion of subjects in each arm to have ingested more than 5 ml/kg of fluid within 30 and 60 minutes from the time of administration of the study mixture; (2) the proportion of subjects in each arm to have ingested more than 10 ml/kg of fluid within 30 and 60 minutes from the time of administration of the study mixture.

#### Longer term

(1) incidence of adverse events (seizures, cardiac arrhythmias and aspiration) within the 90 minute study period; (2) the proportion of subjects who require fluid administration via intravenous line or nasogastric tube (oral hydration failures); (3) the proportion of subjects requiring hospital admission; (4) duration of stay in the ED

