### Patient Randomisation

Patients who fulfil the eligibility criteria and whose parents provide informed consent will be randomised to either 2% viscous lidocaine or placebo.

The randomisation schedule will be computer generated using block randomisation by the Clinical Biostatistics and Epidemiology Unit (CEBU, Murdoch Children's Research Institute, Melbourne, Australia). Random block sizes will be used. The randomisation will not be stratified. Sequentially numbered bottles of either lidocaine or placebo will be arranged according to this schedule by a study pharmacist. Once a patient has been randomised they will be given the next available study number which will equate to an allocation of study drug dispensed in two bottles (labelled Bottle A and Bottle B).

At the time of randomisation patients will be given a dose of study solution from Bottle A which will contain the study drug according to their random allocation. Bottle B will contain the alternative mixture i.e. lidocaine if randomised to placebo and placebo if randomised to lidocaine. After 60 minutes the treating clinician may prescribe a dose from this second bottle if clinically warranted. This ensures that all participants in the study have access to the active treatment.

All study drugs will be packaged in blinded containers stored in a locked cupboard labelled only with the study details and the study number. Only the study pharmacist will be aware of the treatment allocation.

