**Figure 1 F1:**
[figure not shown]
**Study Flow Chart**. The schedule of study observations that will be recorded during the 60 minute study period and the 30 minute observation period. (legend) ED emergency department

After the end of the 60 minute fluid trial and once the outcome data has been collected, the treating clinician will complete a fluid assessment on the participant. At this point, if the treating clinician feels that a participant has not had enough fluid, he/she may decide to:

• Administer the second bottle allocated to that participant (Bottle B) - participants previously given placebo will receive the active drug (i.e. 2% viscous lidocaine), and vice versa, and/or

• Administer other oral analgesia e.g. paracetamol or ibuprofen

The study will terminate at 90 minutes (i.e. 30 minutes after the end of the 60 minute fluid trial for assessment of adverse events) where the participant will be reviewed for signs of aspiration. However, if at any point during the trial the participant starts coughing and/or show other signs of aspiration, he/she will be urgently reviewed by the treating clinician. A completed participant is one who has had the solution administered, and has had their fluid intake monitored for a minimum of 60 minutes from the time of administration of the study mixture. If the participant does not complete the 60 minute study period, the reason for the premature termination will be documented on the CRF. After the completion of the 60 minute trial of fluids routine care will follow as directed by the treating clinician.

Complications recorded will include: allergic reactions (including anaphylaxis), seizures, cardiac arrhythmia, and clinical episodes of aspiration.

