### *The secondary outcome *measures are in 2 groups

#### Short term

those within 60 minutes - and longer term - those between 60 and 90 minutes. Comparisons between groups will only be made in the short term outcomes since both groups will have access to lidoocaine after 60 minutes.

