### Sample size, power and statistical methods

There is currently no published literature on the effectiveness of 2% viscous lidocaine for improving oral fluid intake in painful infectious mouth conditions, hence we carried out a pilot study of 20 patients to document the mean fluid intake and spread of the data.

The data from the pilot study found a mean difference of 4.3 mls/kg (standard deviation = 7 mls/kg) ingested over a 60 minute period between the two treatment groups. Assuming a slightly conservative estimate of the treatment effect of 4 mls/kg (standard deviation = 7), would require a sample size of 50 children per group (100 children in total), based on 80% power and 5% significance. A review of expert clinical opinion (10 paediatric emergency attendings in Melbourne, Australia) concluded that a difference of 4-5 mls/kg represented a clinically important difference.

Based on the recruitment rate in the pilot study (20 participants in 5 months) we expect patient recruitment to take 2 years (the 20 patients from the pilot study will be included in the final analysis). We have not allowed for any loss-to-follow up in this time line as we expect to retain all patients for the 60 minutes needed for the study.

Analysis will be by intention to treat. Data will be analysed descriptively and statistically using the STATA data analysis program. Data for the primary outcome will be reported with an estimate of the difference in means and its 95% confidence interval - obtained using an unadjusted linear regression. Since this is an RCT, and the outcome measure is measured on a continuous scale, the t-test will be used to compare the 2 groups. If necessary due to skewed data, the data will be log-transformed. Secondary outcomes in the short term group will be analysed with t-tests for continuous data and chi-squared tests for categorical data, while the longer term group will have descriptive statistics only. As a sensitivity analysis, all treatment comparisons for primary and secondary outcomes will also be presented adjusted for age at presentation to account for any chance imbalance between the treatment groups with respect to this potentially confounding factor using linear and logistic regression models for continuous and binary outcomes respectively.

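### Adverse events in the first 60 minutes are left out of the between-group comparison for a reason that applies only after 60 minutes

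*Protocol article*

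**What the plan says.** All references are to the protocol article.

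- **Grouping of secondary outcomes.** The secondary outcomes are divided into short term, "those within 60 minutes - and longer term - those between 60 and 90 minutes". The rule for comparison follows: "Comparisons between groups will only be made in the short term outcomes since both groups will have access to lidoocaine after 60 minutes".
- **Short-term list.** It holds only the proportions of children passing 5 and 10 ml/kg at 30 and 60 minutes. No adverse event outcome is in it.
- **Longer-term list.** Its first item is the "incidence of adverse events (seizures, cardiac arrhythmias and aspiration) within the 90 minute study period".
- **Analysis.** Under Sample size, power and statistical methods, short-term outcomes are tested, "while the longer term group will have descriptive statistics only". The same section specifies intention to treat.
- **Second bottle.** Under Patient Randomisation: "After 60 minutes the treating clinician may prescribe a dose from this second bottle if clinically warranted". Its content is the opposite of the first: "Bottle B will contain the alternative mixture i.e. lidocaine if randomised to placebo and placebo if randomised to lidocaine".
- **Events recorded.** Under Study Procedure: "Complications recorded will include: allergic reactions (including anaphylaxis), seizures, cardiac arrhythmia, and clinical episodes of aspiration". The section on Adverse experiences covers all events in both the 60-minute study period and the 30-minute observation period.

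**The concern.** Two things do not fit together. First, the adverse event outcome starts at dosing, yet it sits in a group defined as starting at 60 minutes. Second, that group is excluded from comparison on one ground only, access to lidocaine after 60 minutes, and this ground says nothing about the first hour. Until 60 minutes the arms differ only in the randomised Bottle A, so events in that hour give a clean lidocaine versus placebo contrast. The grouping removes it along with the contaminated half hour.

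At stake is how the safety data will read. The primary outcome and the short-term intake outcomes stop at 60 minutes and are untouched. But a single 0-90 minute incidence combines an hour of pure randomised exposure with half an hour in which some placebo children may have had lidocaine and some lidocaine children placebo. Lidocaine is given here just before a trial of drinking, and the protocol singles out aspiration for review at 90 minutes, so a clear early safety summary is worth having.

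A smaller mismatch is that allergic reactions are among the complications recorded but not among the events named in the outcome.

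**Working it through.** **1. The plan's own figure.** The only design figure is 50 children per group, for a difference of 4 ml/kg, SD 7, 80% power and 5% significance (taken as two-sided). The normal formula gives n = 2 × (1.960 + 0.842)² × (7/4)² ≈ 48.1, so 49 per group. The t-based solution is 49.05, so 50. Power at 50 per group is 81.5% (normal) or 80.8% (t). The figure reproduces. It is used below only as the denominator; the documents give no design figure for adverse events.

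**2. The rules set against the clock.**

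| Period | Study mixture given | Does the stated reason for not comparing apply? | Planned between-group comparison of adverse events |
|---|---|---|---|
| 0-60 min | Bottle A only | No | None |
| 60-90 min | Bottle A, with Bottle B in some children | Yes | None |

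The first row is the defect. It follows from stated rules, not from something left unsaid: the short-term list contains no adverse events, and only short-term outcomes are compared.

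This takes the Bottle B provisions as they stand. The section headed For both groups says no further study mixture is given. That may refer only to the first hour, but it should be reconciled with the Bottle B text.

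**3. What pooling could do, if the table is by randomised arm.** Define, all as assumptions because the documents give no values:

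- p = lidocaine-attributable risk per dose, the same from either bottle, with Bottle A events arising within 60 minutes;
- q = share of the placebo arm given Bottle B;
- f = share of attributable events starting within 30 minutes of the dose, with Bottle B given at 60 minutes;
- background risk = 0.

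Over 0-60 minutes the risks are p and 0, a difference of p. Over 0-90 minutes they are p and q×f×p, a difference of p - q×f×p = p(1 - q×f).

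Share of the difference that remains:

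| q | f = 0.5 | f = 1 |
|---|---|---|
| 0 | 100% | 100% |
| 0.25 | 87.5% | 75% |
| 0.5 | 75% | 50% |
| 0.75 | 62.5% | 25% |
| 1 | 50% | 0% |

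In expected events with 50 per arm, q = 0.5 and f = 1 (50×p under lidocaine, 50×0.5×p under placebo):

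| p | Lidocaine | Placebo, 0-60 min | Placebo, 0-90 min |
|---|---|---|---|
| 0.5% | 0.25 | 0 | 0.125 |
| 2% | 1.0 | 0 | 0.5 |
| 5% | 2.5 | 0 | 1.25 |
| 10% | 5.0 | 0 | 2.5 |

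The Background describes adverse events from topical lidocaine as uncommon, which favours the upper rows. There the proportional dilution is the same, but the counts are too small for it to be seen.

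**4. What a 0-60 minute comparison could show.** With 0 events in 50, the exact two-sided 95% upper limit solves (1 - π)^50 = 0.025, so π = 1 - 0.025^(1/50) = 7.1%. Fisher's exact test gives p = 0.24 for 3 versus 0, 0.056 for 5 versus 0 and 0.027 for 6 versus 0, so at least 6 versus 0 is needed for significance at 5%. Its power is about 4% at true risks of 5% versus 0%, and about 38% at 10% versus 0%.

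**The case against.** The strongest reply is that the protocol has seen the contamination and deliberately draws no inference from it. Descriptive reporting of rare events in 100 children is normal, and table layout belongs to a statistical analysis plan, which the section on Breaking of the Study Blind says will be agreed before unblinding. Events in both periods are captured, so nothing need be lost.

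Much of this stands. Descriptive reporting is not a fault in itself, and a significance test would add almost nothing. What does not stand is the appeal to layout. The protocol states which outcomes are compared and gives a reason, and that reason stops short of the first hour.

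A reader might go further and infer that the plan charges Bottle B lidocaine events to placebo and so biases its safety result. The documents do not support that. No section says how the descriptive data are tabulated, by-arm display is only implied by intention to treat, it would matter only for placebo children who get Bottle B, and no formal contrast is planned that could be biased.

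Nor are allergic reactions lost. They are recorded under Study Procedure and fall within Adverse experiences, so their absence from the outcome is a minor inconsistency. It would also be wrong to say that events after Bottle B are followed for only 30 minutes, because later events thought to be due to a study intervention are included. Finally, the abstract lists adverse events apart from the longer-term outcomes, but it is a condensed list and does not show that a comparison was intended.

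**Conclusion.** The point holds as a fault of window and grouping. The adverse event outcome contradicts the definition of the group that contains it, and a reason valid only after 60 minutes is used to set aside the one uncontaminated randomised safety contrast.

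The possible dilution of a pooled by-arm summary is conditional and of unknown size. It ranges from none (q = 0) to complete masking (q = f = 1), and rests on display by randomised arm, equal risk per dose and no background risk. The matter concerns a secondary safety outcome only. It should be corrected, but it does not threaten the trial's main result.

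**What to change.** 1. Make adverse events from dosing to 60 minutes, before any Bottle B dose, a short-term outcome. Report them by randomised arm with the risk difference and an exact 95% confidence interval. No significance test is required.
2. Tabulate events after 60 minutes separately and descriptively, by sequence received within each arm (Bottle A only, or A then B). Bottle B is given at the clinician's discretion, so this table is not a randomised comparison.
3. Add allergic reactions to the events named in the outcome, to match the complications recorded under Study Procedure.

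The cost is a change of wording and one table. Events are already captured in both periods, but the split needs each event's onset placed before or after 60 minutes and any Bottle B dose. For the 20 pilot children this depends on what their records hold. The downside is limited precision in the 0-60 minute estimate, which the confidence interval will show.

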### Sample size, power and statistical methods

There is currently no published literature on the effectiveness of 2% viscous lidocaine for improving oral fluid intake in painful infectious mouth conditions, hence we carried out a pilot study of 20 patients to document the mean fluid intake and spread of the data.

The data from the pilot study found a mean difference of 4.3 mls/kg (standard deviation = 7 mls/kg) ingested over a 60 minute period between the two treatment groups. Assuming a slightly conservative estimate of the treatment effect of 4 mls/kg (standard deviation = 7), would require a sample size of 50 children per group (100 children in total), based on 80% power and 5% significance. A review of expert clinical opinion (10 paediatric emergency attendings in Melbourne, Australia) concluded that a difference of 4-5 mls/kg represented a clinically important difference.

Based on the recruitment rate in the pilot study (20 participants in 5 months) we expect patient recruitment to take 2 years (the 20 patients from the pilot study will be included in the final analysis). We have not allowed for any loss-to-follow up in this time line as we expect to retain all patients for the 60 minutes needed for the study.

Analysis will be by intention to treat. Data will be analysed descriptively and statistically using the STATA data analysis program. Data for the primary outcome will be reported with an estimate of the difference in means and its 95% confidence interval - obtained using an unadjusted linear regression. Since this is an RCT, and the outcome measure is measured on a continuous scale, the t-test will be used to compare the 2 groups. If necessary due to skewed data, the data will be log-transformed. Secondary outcomes in the short term group will be analysed with t-tests for continuous data and chi-squared tests for categorical data, while the longer term group will have descriptive statistics only. As a sensitivity analysis, all treatment comparisons for primary and secondary outcomes will also be presented adjusted for age at presentation to account for any chance imbalance between the treatment groups with respect to this potentially confounding factor using linear and logistic regression models for continuous and binary outcomes respectively.

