**Inclusion criteria - all of:**
Diagnosed by the treating doctor with ulcerative pharyngitis, herpangina, hand foot and mouth disease, herpetic gingivostomatitis OR non-herpetic gingivostomatitis
Parental complaint of child's poor oral intake
Intake of less than 10 ml/kg of fluid within 2 hours preceding presentation to RCH ED

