### Outcome measures

*The primary outcome *is the amount of fluid ingested by each child, expressed in ml/kg, within 60 minutes from the time of administration of the study mixture.

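### The rule to log-transform the primary outcome if skewed is undefined for a child who drinks nothing and moves the test off the ml/kg scale on which the trial was planned

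*Protocol article*

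**What the plan says.** All but two of the statements below are in the Protocol article, section Sample size, power and statistical methods.

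- The primary outcome, defined under Outcome measures, "is the amount of fluid ingested by each child, expressed in ml/kg, within 60 minutes from the time of administration of the study mixture".
- Effect measure: "Data for the primary outcome will be reported with an estimate of the difference in means and its 95% confidence interval". It comes from an unadjusted linear regression, and the two groups are compared with a t-test.
- Transformation: "If necessary due to skewed data, the data will be log-transformed". No criterion for skewness, no treatment of a zero and no replacement effect measure is given.
- Analysis set: "Analysis will be by intention to treat".
- Planning: "Assuming a slightly conservative estimate of the treatment effect of 4 mls/kg (standard deviation = 7"), giving 50 children per group for 80% power at 5% significance.
- Relevance: a survey of ten emergency physicians "concluded that a difference of 4-5 mls/kg represented a clinically important difference".
- Population (Table 1): "Intake of less than 10 ml/kg of fluid within 2 hours preceding presentation to RCH ED", together with a parental complaint of poor intake.

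**The concern.** The outcome has a floor at zero, and the trial enrols children because they are drinking poorly. The protocol itself expects some to go on doing so: under Study Procedure the clinician may intervene at 60 minutes if intake has been insufficient, and the longer-term outcomes count oral hydration failures. Zero is therefore a possible value, and the least favourable one.

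Two things follow from the log rule without any simulation. First, it cannot be carried out on a zero unless someone decides to exclude the child or to add a constant, and the protocol makes neither decision. Second, it changes the comparison from a difference in ml/kg to a ratio of geometric means, which cannot be set against a 4-5 ml/kg threshold. At stake is the trial's one primary comparison. Its result could turn on a choice made late and not recorded in this document.

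**Working it through.** **1. The plan's own figure.** Inputs: difference 4 ml/kg, SD 7 ml/kg, 80% power, 5% significance (two-sided assumed). n per group = 2 × SD² × (1.960 + 0.842)² / difference² = 2 × 49 × 7.85 / 16 = 48.1, so 49 by the normal approximation. The exact t calculation gives 79.96% power at 49 and 80.8% at 50. The stated 50 per group is reproduced, on the untransformed ml/kg scale.

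**2. Is skew plausible?** The article gives the pilot's difference and SD ("The data from the pilot study found a mean difference of 4.3 mls/kg (standard deviation = 7 mls/kg") but no arm means. If the control mean were 6 ml/kg, a normal distribution with SD 7 would put Φ(−6/7) = 20% of children below zero; at a mean of 10 it would put 8% there. Intake cannot be negative, so right skew is plausible if the means are in that range. Whether they are is not stated.

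**3. Change of scale.** The same gain of 4 ml/kg is a ratio of arithmetic means of (m + 4)/m, where m is the assumed control mean: 8/4 = 2.0, 10/6 = 1.67, 12/8 = 1.5, 14/10 = 1.4. A ratio alone does not show whether 4-5 ml/kg was reached.

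**4. A constructed example of zero handling.** Control: 20 children at 0 and 30 at 10 ml/kg. Lidocaine: 2 at 0, 18 at 2 and 30 at 15.5 ml/kg.

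- Untransformed: means 300/50 = 6.0 and (36 + 465)/50 = 10.0; t-test p = 0.001 in favour of lidocaine.
- Zeros dropped: geometric means 10 and exp[(18 ln 2 + 30 ln 15.5)/48] = 7.19; ratio 0.72, p = 0.08, in the wrong direction.
- log(x + 1): sums of logs 103.88 and 71.94; ratio exp[(103.88 − 71.94)/50] = 1.89.
- log(x + 0.1): sums 91.17 and 23.32; ratio exp(67.84/50) = 3.88.
- log(x + 0.01): sums 85.60 and −23.00; ratio exp(108.60/50) = 8.78.

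One data set gives ratios from 0.72 to 8.78, depending on a decision the protocol does not make.

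**5. Simulated power, 50 per arm.** Assumed: means 6 v 10 ml/kg, SD 7 in both arms, a stated share of zeros, and a gamma or log-normal distribution among drinkers. Entries are the share of trials significantly favouring lidocaine.

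| Zeros, control v lidocaine | Drinkers | Raw t-test | c = 1 | c = 0.1 | c = 0.01 |
|---|---|---|---|---|---|
| 20% v 20% | gamma | about 80% | 73% | 47% | 27% |
| 20% v 20% | log-normal | 79% | 66% | 34% | 19% |
| 10% v 10% | log-normal | 81% | 87% | 62% | 37% |
| 20% v 5% | log-normal | 81% | 97% | 94% | 90% |
| 5% v 20% | log-normal | 80% | 55% | 12% | 2% |
| none | log-normal | 80% | 99% | 99.5% | 99.5% |

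So log(x + c) may lose or gain power, depending on the constant and on where the zeros fall.

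**6. Zeros dropped, in scenarios where lidocaine turns refusers into drinkers.** Assumed: drinkers' intake is gamma with mean 10 and SD 6 ml/kg.

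- (a) Refusers 5% on lidocaine and 45% on placebo; true gain 0.95 × 10 − 0.55 × 10 = 4.0 ml/kg. The raw t-test detects it in about 86% of trials. Dropping zeros loses on average 50 × 0.05 + 50 × 0.45 = 25 of 100 children and shows benefit in about 3%, roughly the chance rate.
- (b) The 40% who would refuse on placebo drink about 4 ml/kg on lidocaine; true gain 0.40 × 4 = 1.6 ml/kg. Dropping zeros significantly favours placebo in about 52% of trials. If they drink about 6 ml/kg (true gain 2.4), it does so in about 21%.
- The same data with log(x + c), c = 1, 0.1 or 0.01: benefit is detected in 99% or more of trials in (a) and in 92-100% in (b), with none significantly favouring placebo. The raw test detects benefit in about 25% and 49% of trials in the two versions of (b).

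Dropping zeros is not always harmful to power either: with equal 20% zeros in the table's setting it detects benefit in nearly every trial. It is then a comparison among drinkers only.

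**The case against.** The strongest reply is that the protocol nowhere says that zeros will be excluded, and that its intention-to-treat statement points the other way. The reversal in step 6 comes from that exclusion. When every child is kept through log(x + c), the same scenarios show no significant reversal and more power than the untransformed test. This stands. A reader might infer that the log rule as written discards refusers and is likely to reverse a real benefit; the documents do not support that.

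A reader might also infer that the rule will probably be triggered, since entry intake is below about 5 ml/kg per hour and the SD is 7. But the entry criterion is a parent-reported ceiling for the two hours before arrival, not the placebo mean during a supervised fluid trial. The zero shares of 40-45% in step 6 have no source in the protocol.

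Three further points can be made in the protocol's favour. The difference in means is promised without condition, so the log sentence may be meant for the test only; even then the p-value and the reported interval would answer different questions. Unblinding follows agreement of the analysis plan and database lock (Breaking of the Study Blind), so skew could be judged blind to arm; that limits the scope for choosing on results but does not settle the zeros. And an unseen analysis plan may supply the missing details. It may, but the log rule is stated here for the primary outcome, and as stated it cannot be applied to a value the outcome can take. That is a rule fixed badly, not a detail left out.

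**Conclusion.** The concern holds in a limited form. Three things follow from the text alone: the log is undefined at zero, dropping the affected children would conflict with intention to treat, and a log-scale comparison leaves the additive scale of the planned estimate, the sample size and the important difference.

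The size is conditional. With equal 20% zeros, means of 6 v 10 and SD 7, a constant of 1, 0.1 or 0.01 takes power from about 80% to about 73%, 47% or 27%; other assumed patterns raise it above the untransformed test. A missed or reversed benefit is possible if zeros are dropped and lidocaine turns refusers into drinkers of small volumes. With zeros kept, the wrong direction became common only with a very small constant and more refusers on lidocaine: at 5% v 20% zeros and c = 0.01 the sign was wrong in 58% of trials. The protocol reports neither arm means nor a share of zeros, so none of these figures predicts what this trial would show.

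**What to change.** Delete the log-transformation sentence for the primary outcome. State instead that the primary estimate is the difference in mean ml/kg over all randomised children, with no intake counted as 0, whatever the shape of the data. Give it a 95% confidence interval that does not rely on equal variances or normality (Welch, heteroscedasticity-consistent or bootstrap) and a test that matches the interval. If a rank-based or log analysis is wanted, name it as a prespecified sensitivity analysis and state how zeros enter it, including any constant.

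The cost is a sentence or two and no extra patients. The downside is that under skew the untransformed comparison may be less powerful than a log analysis, as the rows with no zeros and with fewer zeros on lidocaine show. The stated 80% power was, however, computed for the untransformed difference.
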